### Interventions

Participants will complete an initial patient questionnaire focusing on demographic and fertility data. This baseline data are collected and managed using REDCap electronic data capture tools hosted at The University of Melbourne.^29
30^ REDCap is a secure, web-based software platform designed to support data capture for research studies, providing (1) an intuitive interface for validated data capture; (2) audit trails for tracking data manipulation and export procedures; (3) automated export procedures for seamless data downloads to common statistical packages and (4) procedures for data integration and interoperability with external sources. Additional clinical information will be collated by the research assistant team, ensuring systematic documentation of endometriosis imaging and/or prior surgical findings, prior fertility investigations (if relevant) and choice of management pathway.

A mobile phone application (known as an ‘App’) has been developed as a data collection tool specific to this study—the ELFS App. The original App was free for participants to download from the Apple App Store and Google Play (December 2021—November 2024). A newly developed version of the ELFS App is designed as a Progressive Web App which is installed on the participants’ mobile device as an application but is deployed by, and retains the functionality of, a website. Transition to the new App occurred over a fortnight period in November 2024. Participant data and survey responses from the first system were exported, then custom scripts used to transform and validate the information before importing it into the new App platform.

Participants are assisted by the study team to set-up the App, which is then used for cyclical survey data collection. Participants complete a monthly/cyclical questionnaire via the mobile App (or they may choose to complete via the online website) to record information about: (a) pregnancy status; (b) whether or not conception was attempted; (c) method of attempt and (d) outcome of pregnancy (if relevant). The participants also complete a menstrual calendar (on the original ELFS App) or a menstrual symptom questionnaire (on the new ELFS App 2.0) each cycle. If the participant does not complete the questionnaire, an SMS or email reminder will be sent to them after 3 days of inactivity. If the questionnaire is still not completed, a second reminder will be sent after a further 3 days. If there is no response after these two reminders, the cycle will be ‘skipped’. If a participant does not complete a survey for three consecutive months, they will be contacted by the research team to confirm their intention to continue within the study.

A study-specific, cycle-based questionnaire was designed to capture (1) detailed menstrual-cycle characteristics and related events (eg, cycle duration and regularity, intercourse timing, pregnancy attempts and contraceptive use), (2) relationship and demographic factors relevant to conception and (3) reproductive outcomes including conception and live birth. Because existing validated instruments do not, to our knowledge, combine these two aims in a brief, per cycle format, we created an adaptive (logic-driven) instrument that presents only questions relevant to each participant in a given cycle. The instrument is intentionally concise because surveys are administered frequently (approximately monthly) and the primary outcomes of the study are conception and obstetric endpoints rather than comprehensive symptom profiling.

Menstrual-cycle symptoms are measured using a simple, 4-point Verbal Rating Scale (VRS) for pain intensity (no pain/mild pain/moderate pain/severe pain) accompanied by pictograms to improve respondent interpretation and reduce response burden. VRSs are widely used and have demonstrated acceptable validity and reliability for clinical pain intensity assessment compared with other pain measures (eg, Visual Analogue and Numeric Rating Scales) and are well suited to brief, repeated measurement in field studies.^32^ A brief 4-point VRS was included rather than longer symptom inventories because more comprehensive menstrual symptom instruments (eg, the Menstrual Distress Questionnaire and other multi-item menstrual symptom scales) are lengthy and were not feasible for monthly administration in a fertility cohort in which the principal outcomes are reproductive.^33^ The questionnaire items and the VRS pain measure were selected to maximise face validity, minimise respondent burden, and enable longitudinal linkage of symptom reports to timing of intercourse, ovulation windows, pregnancy test results and pregnancy outcomes.

The accuracy of participant-entered clinical data is safeguarded by the structured nature of the study-specific questionnaires and real-time front-end checks to prevent entry errors, automated rules that flag implausible or inconsistent responses for in-app confirmation and staff follow-up for clarification. Where participants consent, medical records will be reviewed to verify key outcomes such as surgical reports. For those undergoing surgery during the study period, surgical reports will be collected and assessed by one of two investigators (SM and VR); any disagreements will be clarified by investigator MH. The primary outcome, LBR, is assessed by patient reported data (via the ELFS App) and cross-validated against obstetric outcome data retrieved from the hospital in which the birth occurs. Similarly, CPR is assessed by patient report, and validated by review of first trimester sonographic report. Sensitivity analyses excluding unverified outcomes and analyses of agreement with medical records may be required. Reassuringly, several studies have supported the ability of patients to accurately report their reproductive history, particularly with regards to surgical interventions, fertility treatments and pregnancy outcomes.^34
35^

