#### Primary outcome

LBR (live birth/number of attempted cycles)—‘live birth’ will be defined as birth of a live infant >20 weeks gestation.

For women with EMSE who are attempting natural conception, the ‘per cycle’ LBR will be compared between conservatively or surgically managed groups.

For women with EMSE and infertility who are undergoing IVF, the ‘per cycle’ LBR will be compared between conservatively or surgically managed groups.

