### Power calculation and planned analysis

The target sample size was determined by a simulation-based power calculation. Data were simulated based on a mixed effects logistic regression model with a single fixed effect for treatment and a single random effect for participant. Different random effect SD of 0.5, 0.7 and 0.9 were considered, based on previous studies reporting random effects with SD around 0.7.^36^ Simulations used 5 cycles per participant for natural conception and 3 cycles per participant for IVF. For each set of simulation parameters, 1000 data sets were generated, mixed effects logistic regression models were fitted, and the power was calculated as the proportion of models where the p value for the main effect was below 0.05. The simulation was done using R V.4.0.2, with the glmmTMB package used to fit the mixed effects logistic regression models.

Natural conception based LBR of 1.4% per cycle has been reported in women with moderate to severe endometriosis and 12 months of unsuccessfully trying.^37^ An increase to at least 4% is needed to be clinically significant.^6^ A sample size of N=400 (200 per arm) would achieve over 90% power under the scenarios considered.

An IVF conception-based LBR of 12% per cycle has been reported in women with moderate to severe endometriosis.^38^ An increase to 20% would be needed to be clinically significant. A target sample size of N=300 (150 per arm) would achieve a power of 82% to 87% under the scenarios considered.

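### Verification is described only for reported births and pregnancies, so excluding unverified outcomes would drop events, keep failed cycles, and shift the odds ratio if verification differs between groups

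*Protocol article*

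**What the plan says.** The article's Interventions section makes participant report through the app the basis of both fertility outcomes and adds a record check for each. Live birth is "cross-validated against obstetric outcome data retrieved from the hospital in which the birth occurs". For the secondary outcome, "CPR is assessed by patient report, and validated by review of first trimester sonographic report". Record review is conditional on consent: "Where participants consent, medical records will be reviewed to verify key outcomes such as surgical reports". The section then adds: "Sensitivity analyses excluding unverified outcomes and analyses of agreement with medical records may be required".

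The Primary outcome section takes attempted cycles as the denominator of the live birth rate. The Power calculation and planned analysis section makes discrete-time survival analysis primary and mixed effects logistic regression on cycles a sensitivity analysis. No verification share is given, overall or by group. The article does not say whether excluding an outcome drops the cycle, recodes it or drops the woman.

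**The concern.** Both named sources come into being only after a pregnancy or a birth. A cycle reported as unsuccessful has no source assigned to it, so it cannot fail verification. An exclusion applied to unverified outcomes therefore acts on the numerator and leaves the failed attempts in the denominator, which is selection on the dependent variable. In the survival model the effect is that a woman with an unverified birth keeps her earlier failed cycles and loses the cycle in which she succeeded.

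This analysis would be read as evidence that the result is robust to self-report error. If the chance of obtaining a record differs between surgically and conservatively managed women, it could instead show a difference that is not there or remove one that is. The groups are not randomised, record review depends on consent, and recruitment spans public hospitals, private rooms, IVF clinics and an overseas site, so equal shares cannot be taken for granted.

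**Working it through.** **Inputs from the article (Power calculation and planned analysis).** Natural conception: "Natural conception based LBR of 1.4% per cycle has been reported"; "An increase to at least 4% is needed to be clinically significant"; 200 per arm, 5 cycles each. IVF: 12% rising to 20% per cycle, 150 per arm, 3 cycles each. Random-effect SD 0.5, 0.7 and 0.9; p below 0.05, taken as two-sided. The verified shares below are assumptions.

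**Reproducing the stated power.** Random-intercept logistic simulations, 600 data sets per scenario, gave these results:
- Natural conception: 94% to 95% if the stated rates are read as marginal, 97% to 99% if conditional. The article says "A sample size of N=400 (200 per arm) would achieve over 90% power under the scenarios considered".
- IVF: 84% to 87% (conditional) or 85% to 90% (marginal), against the stated 82% to 87%.

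The design figures are sound and serve as the base for what follows.

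**Effect of the exclusion.** Let p be the true per-cycle rate and v the share of events verified. Dropping unverified event cycles gives

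p' = pv / (pv + 1 − p), so p'/(1 − p') = v × p/(1 − p).

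The odds are multiplied by v, and the surgical/conservative odds ratio by vS/vC. For IVF at 12%:
- v = 0.95: 0.114 / (0.114 + 0.88) = 11.5%
- v = 0.80: 0.096 / (0.096 + 0.88) = 9.8%
- odds ratio 0.95/0.80 = 1.19; rate ratio 1.17

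**No true effect, by assumed verified share**

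| Verified: conservative / surgical | Odds ratio | IVF, true 12%: conservative vs surgical | Natural, true 1.4%: conservative vs surgical |
|---|---|---|---|
| 80% / 80% | 1.00 | 9.8% vs 9.8% | 1.12% vs 1.12% |
| 80% / 95% | 1.19 | 9.8% vs 11.5% | 1.12% vs 1.33% |
| 70% / 90% | 1.29 | 8.7% vs 10.9% | 0.98% vs 1.26% |
| 70% / 95% | 1.36 | 8.7% vs 11.5% | 0.98% vs 1.33% |
| 60% / 90% | 1.50 | 7.6% vs 10.9% | 0.84% vs 1.26% |

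With cycles treated as independent, the chance of a significant result under the null is 5% at equal shares. At 70%/90% it is about 9% (natural) and 20% (IVF), and at 60%/90% about 15% and 42%.

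**At the design rates.** The true odds ratios are (0.04/0.96)/(0.014/0.986) = 2.93 for natural conception and (0.20/0.80)/(0.12/0.88) = 1.83 for IVF.
- Both groups 80% verified: odds ratios unchanged. Rates fall from 1.4% to 1.12%, 4% to 3.23%, 12% to 9.8% and 20% to 16.7%. Independent-cycle power falls from 95% to 90% (natural) and 91% to 86% (IVF).
- Conservative 70%, surgical 90%: odds ratios rise to 3.77 and 2.36.
- Conservative 90%, surgical 70%: odds ratios fall to 2.28 and 1.43.

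**Is the asymmetry the cause?** If failed cycles were also verified, at share u, then p' = pv / (pv + (1 − p)u). With v = u = 0.80, 12% stays 12% and 20% stays 20%. The distortion comes only from verifying one side.

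**If the woman, not the cycle, is dropped.** Dropping a woman because her birth is unverified is still selection on the outcome. The same formula applies with p read as the proportion of women who have a birth.

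**The case against.** The strongest reply is that nothing has been fixed. The sentence says such analyses may be needed and names neither a unit nor a coding rule, and an analysis plan that is not shown may settle both. Consent is given by the participant, so exclusion by participant is a possible reading, and it would remove failed cycles too. The primary analysis is untouched, and agreement with records is named alongside as a second check.

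Much of this stands and limits the point to a conditional one. But the criticism is not of missing detail. The article says that unverified outcomes are what would be excluded, and it assigns verification only to positive ones. A restriction to consenting women would be a different analysis from the one it names.

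Two stronger readings are tempting and not supported:
- A reader might infer that the exclusion necessarily manufactures a difference. It does not: with equal shares the odds ratio is unchanged, and the article gives no evidence that shares differ. It takes birth data from the hospital of birth, not the surgical unit, and describes one study-wide protocol with central data capture.
- A reader might infer that failed cycles can have no record. A failed IVF cycle is a treatment cycle whose clinic record could be sought, and a pregnancy without a live birth may have a scan report. The article simply names no such check for unsuccessful cycles.

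**Conclusion.** The point holds in conditional form. As verification is described, excluding unverified outcomes removes events and keeps failures, and multiplies the odds ratio by vS/vC. With no true effect that means 1.19 at 95% versus 80% verified and 1.36 at 95% versus 70% (surgical versus conservative). On the rate scale the corresponding IVF ratios at 12% are 1.17 and 1.32. With equal shares the only loss is in rates and power.

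The result rests on three assumptions: the exclusion is made on the outcome, failed cycles remain unverified, and the verified share is constant within a group. The shares themselves are illustrative. The primary analysis is not affected. What is at risk is the meaning of a check on self-report in the primary outcome.

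**What to change.** Replace the exclusion with a restriction at participant level that does not depend on the outcome:

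1. Repeat the primary analysis in all women who consented to record access, with consent status taken as recorded before the outcome is known.
2. Keep all their cycles, with or without a birth, and keep any birth that could not be verified as self-reported.
3. Report the share verified and the agreement with records separately for the surgical and conservative groups, within natural conception and IVF.
4. Where records are already accessible, for example at the treating IVF clinic, check reported failures as well as reported successes.

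The cost is a short change of wording, a tabulation by group and a limited number of look-ups in records already open to the team. The downside is a smaller set for this sensitivity analysis, and one that represents consenting women only. A search of records for every participant is not needed for the core correction.

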### Power calculation and planned analysis

The target sample size was determined by a simulation-based power calculation. Data were simulated based on a mixed effects logistic regression model with a single fixed effect for treatment and a single random effect for participant. Different random effect SD of 0.5, 0.7 and 0.9 were considered, based on previous studies reporting random effects with SD around 0.7.^36^ Simulations used 5 cycles per participant for natural conception and 3 cycles per participant for IVF. For each set of simulation parameters, 1000 data sets were generated, mixed effects logistic regression models were fitted, and the power was calculated as the proportion of models where the p value for the main effect was below 0.05. The simulation was done using R V.4.0.2, with the glmmTMB package used to fit the mixed effects logistic regression models.

Natural conception based LBR of 1.4% per cycle has been reported in women with moderate to severe endometriosis and 12 months of unsuccessfully trying.^37^ An increase to at least 4% is needed to be clinically significant.^6^ A sample size of N=400 (200 per arm) would achieve over 90% power under the scenarios considered.

An IVF conception-based LBR of 12% per cycle has been reported in women with moderate to severe endometriosis.^38^ An increase to 20% would be needed to be clinically significant. A target sample size of N=300 (150 per arm) would achieve a power of 82% to 87% under the scenarios considered.

Demographic continuous variables will be compared using the Welch t-test. Proportions will be compared using χ^2^ test. P values below 0.05 will be considered statistically significant. The primary analysis will use discrete-time survival analysis to compare time to pregnancy and time to live birth between the two treatment groups, using inverse probability weighting to account for non-random dropout.^39^ As a sensitivity analysis, mixed effects logistic regression models will also be used to compare clinical pregnancy and LBRs between the two treatment groups, allowing for repeated measures (multiple cycles of attempted conception) within individual participants. Both approaches will adjust for expected confounders, including length of infertility, age, parity, gravidity, indicators of male-factor infertility on semen analysis and selected comorbidities. As this is a multisite study, between-site heterogeneity will be addressed analytically by incorporating site-level random effects. Missing data will be accounted for using multiple imputation by chained equations. The results from a complete case analysis will also be reported, as a sensitivity analysis.

A single, study-wide protocol has been implemented across all participating sites with uniform inclusion/exclusion criteria, standardised outcome definitions, specified data collection schedules (baseline, monthly cycle and operation questionnaires), imaging criteria for moderate/severe endometriosis, and centralised data capture via REDCap and the ELFS App to reduce risks of heterogeneity that could compromise internal validity and to minimise potential bias. Core datasets will be harmonised through project-specific REDCap baseline questionnaires and ELFS App cyclical questionnaires, with prespecified systematic reporting of imaging and surgical findings. All recruitment team members will receive centralised training on eligibility screening, participant interactions and ELFS App setup to ensure consistent participant engagement. Central monitoring will be conducted by the coordinating principal investigator and trials coordinator, supported by real-time recruitment and data-collection dashboards and calculators within the ELFS App.

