**Methods and analysis:**

The Endometriosis Longitudinal Fertility Study (ELFS) is a multisite prospective longitudinal cohort study, recruiting patients <38 years of age with evidence of moderate or severe endometriosis (revised American Society of Reproductive Medicine grades 3 or 4) who desire fertility immediately or in the near future. ELFS aims to longitudinally assess clinical pregnancy and live birth rates for women with moderate or severe endometriosis who choose to have no treatment, fertility treatment and/or surgery. The target sample size was determined by a simulation-based power calculation. The study will comprise 700 participants: 400 attempting natural conception and 300 attempting to conceive with ART. Each of these cohorts will be divided evenly between the conservative and surgical management groups. Following consent and baseline questionnaire, participants instal the purpose-built ELFS App to their mobile phone. The participant then receives cyclical surveys at intervals based on their menstrual cycle, with timing dependent on learnt logic from prior responses. Participants conclude participation following a live birth beyond 20-week gestation. The primary research outcome is to compare the ‘per cycle’ clinical pregnancy rate and live birth rate where endometriosis is managed conservatively or surgically in those conceiving naturally or with assisted reproductive techniques. Secondary outcomes include exploring menstrual cycle characteristics and examining the obstetric outcomes of women with moderate and severe endometriosis who successfully conceive. The outcomes of this research aim to contribute to improving endometriosis management for women desiring pregnancy by establishing if there is a fertility benefit of prepregnancy surgery in patients with moderate or severe endometriosis.

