## Discussion

At present, it is unclear whether prepregnancy surgery for moderate or severe endometriosis, either in the setting of established infertility or even before a woman has begun trying to conceive, confers any benefit in terms of spontaneous or ART conception, live birth or other obstetric outcomes. The outcomes of this research aim to improve endometriosis management for women desiring pregnancy by establishing if there is a fertility benefit of prepregnancy surgery in patients with moderate or severe endometriosis.

Other authors are aiming to investigate the relationship between endometriosis, surgery, and subsequent fertility. To date, we are aware of three international randomised controlled trials currently recruiting. Ottolina *et al*^40^ plan to randomise infertile patients to either surgery (followed by attempts to spontaneously conceive) or IVF. They plan a pragmatic intention to treat analysis. The investigators hypothesise surgery will have a favourable outcome on pregnancy rate, but that IVF will be more successful, and have powered their study based on a 30% LBR in the surgery arm and 50% LBR in the IVF arm. In the Impact of Operation on Fertility for Women With Severe Endometriosis study,^41^ Raos *et al* plan to compare the impact of surgery and ART on fertility for women with deep infiltrating endometriosis of the rectosigmoid. The investigators will compare CPR and LBR 18 months after first-line surgery and first-line ART. In both these studies, investigators have anticipated highly favourable pregnancy rates in a population with either known infertility or high risk of subfertility,^15
17
42–44^ and have not considered the potential impact of comorbid adenomyosis in further reducing fecundity.^17
42
45
46^ The third randomised trial, the ENDOFERT Study, registered by Collinet *et al*^47^ (ClinicalTrials.gov reference number NCT02948972) continues to recruit. This study is randomising infertile participants to either surgery plus post-operative IVF or IVF alone, aiming to examine if pre-IVF surgery improves pregnancy rates.

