While these trials will provide important randomised evidence on surgery versus ART in selected infertile or high-risk groups, their restrictive eligibility, omission of natural conception arms and lack of systematic assessment of comorbid adenomyosis limit generalisability. Moreover, these three study designs anticipate that participants will be willing to be randomised despite the scientific equipoise. Many patients with severe endometriosis, even in the absence of colorectal or urological obstruction (both of which are exclusion criteria in these randomised trials), will be highly symptomatic, and despite fertility desires, will actively pursue surgery in the hope of symptom control. These studies underscore the need to also measure natural time-to-pregnancy and spontaneous conception rates, and to adopt a broader, real-world design that captures symptom burden and patient treatment preferences alongside fertility outcomes.

Alongside these important ongoing randomised studies, ELFS aims to compare fertility outcomes for those who have moderate or severe endometriosis pursuing either natural or ART conception, including both those who undergo preconception surgery and those who are conservatively managed, with cross-comparisons between all four groups. The large sample size and pragmatic observational approach have, to date, demonstrated feasible recruitment.

This study has several important potential limitations. The primary outcome requires a large participant sample, but strict inclusion criteria to ensure accurate diagnosis of moderate and severe endometriosis may considerably restrict the eligible population. This could slow recruitment, reduce statistical power if target numbers are not met, and introduce selection bias, which in turn may limit applicability beyond specialist endometriosis care settings.

Furthermore, the repeated collection of sensitive data, including sexual history, fertility and pregnancy outcomes, may negatively affect participant experience and engagement. The burden and intrusiveness of such assessments could lead to distress, underreporting of sensitive information, and differential loss to follow-up, with potential for missing and biased data. Together, these factors may affect both the internal and external validity of the study’s findings.

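### The named confounders include no measure of endometriosis extent, so the self-selected surgery comparison risks confounding by severity; baseline imaging phenotype should be added

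*Protocol article*

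**What the plan says.** ELFS is a prospective cohort without randomisation. The abstract describes women "who choose to have no treatment, fertility treatment and/or surgery".

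Under Power calculation and planned analysis, the primary analysis is a discrete-time survival model and the sensitivity analysis is a mixed effects logistic model. On adjustment the section says: "Both approaches will adjust for expected confounders, including length of infertility, age, parity, gravidity, indicators of male-factor infertility on semen analysis and selected comorbidities". The only weighting it states is "using inverse probability weighting to account for non-random dropout".

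The Discussion says that many patients with severe endometriosis "will be highly symptomatic, and despite fertility desires, will actively pursue surgery in the hope of symptom control". It also remarks that two ongoing randomised trials "have not considered the potential impact of comorbid adenomyosis in further reducing fecundity".

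On data, the Interventions section describes the research team "ensuring systematic documentation of endometriosis imaging and/or prior surgical findings, prior fertility investigations (if relevant) and choice of management pathway". The baseline form is described thus: "Participants will complete an initial patient questionnaire focusing on demographic and fertility data". Pain appears as a per-cycle item: "Menstrual-cycle symptoms are measured using a simple, 4-point Verbal Rating Scale (VRS) for pain intensity".

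**The concern.** When women and their clinicians choose the management, a variable confounds the comparison if it bears on both that choice and the chance of a live birth. How extensive the endometriosis is (endometrioma on one or both sides, deep disease, an obliterated pouch of Douglas) is the obvious candidate. It is a feature of the index disease, so it does not read naturally as a comorbidity, and it is not among the variables named.

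Restricting entry to moderate or severe disease narrows the range of severity but does not remove it. The inclusion criteria admit both rASRM stages and several distinct phenotypes.

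The study exists to establish whether surgery before pregnancy helps fertility. If surgery draws the more severe cases, a real benefit can be hidden or an apparent harm created. If it draws the milder, more operable cases, a benefit can be manufactured.

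**Working it through.** **1. The sections side by side.**

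- Choice of management: self-selected (abstract). Symptoms in severe disease are named as a reason for surgery (Discussion).
- Spread of severity: stages 3 and 4, ovarian cysts and deep disease or its hallmarks all qualify (Inclusion criteria).
- A measure shared by both arms: rASRM concordance will be checked only in the surgical subgroup (text under Exclusion criteria), so operative stage is not planned for everyone. Imaging and/or prior surgical findings are documented for the cohort (Interventions).
- Named adjustment: fertility history, age, male factor and undefined comorbidities. Extent is not named.

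**2. The plan's own power figures.** Inputs from the power section: random-effect SD 0.5, 0.7 and 0.9; 5 natural or 3 IVF cycles; alpha 0.05, taken as two-sided. A re-simulation used 1000 data sets per scenario and a random-intercept logistic model.

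| Cohort | Stated | Rates read as conditional | Rates read as marginal |
|---|---|---|---|
| Natural, 1.4% v 4%, 200 per arm | over 90% | 97.7–98.0% | 93.5–94.8% |
| IVF, 12% v 20%, 150 per arm | 82–87% | 80.4–89.3% | 85.4–88.5% |

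The natural figure reproduces. The IVF range is matched within about 2 to 3 points, depending on how the rates are read. These figures are not in dispute, but the simulation model holds only treatment and a participant effect, so it assumes no confounding.

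**3. Apparent effect when there is none.** All inputs here are assumptions. Let a share s of an arm have severe disease, and let severe disease divide the per-cycle rate by r. The arm's rate is proportional to 1 − s + s/r.

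- 60% surgical v 40% conservative, r = 2: 0.70/0.80 = 0.88
- 60% v 40%, r = 3: 0.600/0.733 = 0.82
- 70% v 30%, r = 2: 0.65/0.85 = 0.76
- 70% v 30%, r = 3: 0.533/0.800 = 0.67 (1.40% v 0.93% per cycle)

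Swap the arms and the ratios become 1.14, 1.22, 1.31 and 1.50.

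**4. The same idea in the planning model.** One unadjusted binary factor was added (SD 0.7, conditional rates, 400 data sets per scenario), more common in the surgical arm. The bias factor is (p_s·OR + 1 − p_s)/(p_c·OR + 1 − p_c). Without the factor, power at SD 0.7 is about 86% (IVF) and 98% (natural).

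| Share, surgery v conservative | Factor OR | Bias factor | IVF OR (true 1.83) | IVF power | IVF rejection, no effect | Natural OR (true 2.93) | Natural power |
|---|---|---|---|---|---|---|---|
| 60 v 40 | 0.7 | 0.93 | 1.71 | 73% | 6.5% | 2.73 | 94% |
| 60 v 40 | 0.5 | 0.875 | 1.60 | 63% | 8% | 2.51 | 91% |
| 70 v 30 | 0.7 | 0.87 | 1.57 | 60% | 12.5% | 2.59 | 91% |
| 70 v 30 | 0.5 | 0.765 | 1.37 | 32% | 21% | 2.23 | 74% |

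The excess IVF rejections lie in the direction of harm from surgery. This is the mixed model used for planning and for the sensitivity analysis, not the primary survival model.

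**5. Events available for a longer covariate list.**

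- Natural cohort, all cycles used: 1000 × 0.014 + 1000 × 0.04 = 54 live births. Stopping at a birth, with no random effect: 200 × (1 − 0.986⁵) + 200 × (1 − 0.96⁵) = 13.6 + 36.9 = about 51.
- IVF cohort, stopping at a birth: 150 × (1 − 0.88³) + 150 × (1 − 0.80³) = 47.8 + 73.2 = about 121.

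At one parameter each, the six named items plus treatment make 7. Endometrioma laterality (2), deep disease, pouch obliteration and previous surgery add 5. That makes 12 before any time terms, or about 51/12 = 4 events per parameter in the natural cohort.

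**The case against.** The strongest reply is that the list is introduced as a set of examples, and that a journal article may leave the full covariate list to a protocol or SAP not shown here. That stands against any claim that the plan excludes disease extent. It does not dispose of the point: the article does set out its expected confounders, and it leaves out the extent of the index disease while describing selection into surgery among symptomatic patients with severe disease.

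Other parts of the reply also stand:

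- **Adenomyosis.** The article itself treats it as a comorbid condition, so it may well be covered. What is lacking is a statement that it is.
- **Previous surgery.** The Introduction describes the conservative groups as having had none, which deals with part of it. But the Study groups section defines that arm by planned non-surgical management, and the exclusion criteria do not mention earlier operations.
- **Pain.** The documents link symptoms to choosing surgery, but not to fertility independently of extent. A pre-management pain score is not shown to exist, and pain rated after surgery may be a result of it.
- **Ovarian reserve.** It is not shown to be collected at baseline, and a value taken after surgery could lie on the causal path.
- **Named covariates.** Length of infertility may carry part of the severity effect. The illustrations assume that it carries none.
- **Weighting.** Covariate adjustment is itself a legitimate way to handle treatment choice. That the stated weights serve only dropout is not a fault.

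A reader might infer that the surgery effect will be confounded, or that surgery will be made to look worse than it is. The documents support neither. They give no prevalence of severity by arm and no effect of extent on live birth within the eligible range.

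**Conclusion.** The point holds as a risk in the text as written. The comparison is non-randomised, the cohort spans a range of disease extent, the article gives a reason why severe, symptomatic cases may go to surgery, and the confounders it names include no measure of extent. The measure that would help is already documented systematically.

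The size is not known. The rate ratios of 0.88 to 0.67 under no effect rest wholly on assumed prevalences and effects of severity, and they turn into 1.14 to 1.50 if the worse-prognosis women are managed conservatively. The fall in IVF power to between 73% and 32% rests on the same kind of assumption. These figures show why the matter deserves settling; they do not estimate the bias in this study. The stated power figures stand on their own terms.

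**What to change.** In the adjustment sentence, for both the discrete-time survival model and the mixed model:

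1. Add imaging phenotype recorded before management begins: endometrioma (none, one side, both), deep disease (yes/no) and pouch of Douglas obliteration (yes/no).
2. State that the selected comorbidities include adenomyosis where imaging records it.
3. Add previous endometriosis surgery where recorded.
4. Add pain only if a value from before management exists, and say where it is captured.

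With about 50 live births expected in the natural cohort, entering every term directly would be thin. A propensity score for management group is one acceptable way to carry the set. If it is used as a weight, multiply it by the dropout weight and state the target population, since overlap weights change it. Whichever route is taken, report baseline balance between the arms as standardised differences.

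The cost is plan wording, coding of phenotype from reports already gathered, modelling time and a small loss of precision. Women who entered on a previous laparoscopy may have surgical findings in place of imaging, so the coding rule should cover both sources. The list should be fixed before outcomes are compared by management group.
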